# Appendices

## Appendix I. Sample size calculations

The sample size calculation is based on the comparison of two receiver operator characteristic curves (ROC), 2-sided test, with alpha=0.05. The assumed AUC for the RCRI, age, and MINS model is 0.55 (AUC1). The assumed AUC of the frailty assessment model is between 0.65-0.75 (AUC2). The assumed AUC difference is approximately 0.13. We expect an incidence of the primary outcome (all-cause death or disability at 6 months after surgery) to be 20%.

A sample size of 250 patients will give us at least 80% of power to detect a difference of at least 0.130 in the AUC for a model including only the FP-frailty assessment, compared with the AUC for the model including preoperative RCRI and age combined with MINS.

The assumed correlation between the two predictive models is 0.50 for the positive group (those experiencing the outcome) and 0.50 for the negative group (those not experiencing the outcome)

We will include 280 patients to conservatively account for ≤10% who will be lost before or during surgery, or in whom biomarker measurement will not be possible.

Software: PASS 13 (NCSS, LLC. Kaysville, Utah, USA. [www.ncss.com](http://www.ncss.com))

Sample size calculation

| AUC1 | AUC difference | AUC2 | Target power | Sample size |
|------|----------------|------|--------------|-------------|
| 0.55 | 0.10           | 0.65 | 80%          | 405         |
| 0.55 | 0.10           | 0.65 | 85%          | 465         |
| 0.55 | 0.10           | 0.65 | 90%          | 545         |
| 0.55 | 0.13           | 0.68 | 80%          | 240         |
| 0.55 | 0.13           | 0.68 | 85%          | 280         |
| 0.55 | 0.13           | 0.68 | 90%          | 325         |
| 0.55 | 0.15           | 0.70 | 80%          | 185         |
| 0.55 | 0.15           | 0.70 | 85%          | 210         |
| 0.55 | 0.15           | 0.70 | 90%          | 245         |
| 0.60 | 0.10           | 0.70 | 80%          | 425         |
| 0.60 | 0.10           | 0.70 | 85%          | 485         |
| 0.60 | 0.10           | 0.70 | 90%          | 570         |
| 0.60 | 0.13           | 0.73 | 80%          | 250         |
| 0.60 | 0.13           | 0.73 | 85%          | 290         |
| 0.60 | 0.13           | 0.73 | 90%          | 340         |
| 0.60 | 0.15           | 0.75 | 80%          | 190         |
| 0.60 | 0.15           | 0.75 | 85%          | 220         |
| 0.60 | 0.15           | 0.75 | 90%          | 255         |

## Appendix II. Clinical outcomes definitions

The following list provides the definitions for the clinical outcomes for which the predictive ability of perioperative frailty and cardiovascular risk assessments will be assessed in the study.

### New disability (at 28 days, 6 months, or 1 year after surgery)

Disability status is determined using the 12-item World Health Organization Disability Assessment Schedule (WHODAS 2.0). New disability at any time point is based according to the following criteria that account for baseline disability scores:

1. For individuals with a disability score of <25% at baseline, new disability is defined as a disability score ≥25% at follow-up;

2. For individuals with a disability score  $\geq 25\%$ , new disability is defined as an increase in disability score of  $\geq 8\%$ .

Definition of new disability at 28 days, 6 months, and 1 year after surgery will use as baseline disability score the WHODAS 2.0 score measured before surgery.

### **Sub-classification of death**

Vascular death is defined as any death with a vascular cause and includes those deaths following a myocardial infarction, cardiac arrest, stroke, cardiac revascularization procedure (i.e., percutaneous coronary intervention [PCI] or coronary artery bypass graft [CABG] surgery), pulmonary embolus, hemorrhage, or deaths due to an unknown cause. Non-vascular death is defined as any death due to a clearly documented non-vascular cause (e.g. trauma, infection, malignancy).

### **Oncologic outcomes (at 6 and 12 months)**

They will include:

1. PFS, defined as the time from treatment initiation to tumor progression or recurrence or death from any cause, or to the date of censoring at the last time the subject was known to be alive.
2. Cancer-specific death is death directly attributable to the primary gynecological cancer or directly related to its treatment, in the absence of other causes of death.

For the purpose of this study and the evaluation of frailty predictive performance, treatment initiation will be first defined as the time of surgery, and the evaluated frailty assessment will be the one done before surgery (even in patients who had NACT). Secondarily, treatment initiation will be defined as initiation of any cancer-specific treatment, whether NACT or surgery, and the evaluated frailty assessment will be the one done before the first cancer-specific treatment, whether NACT or surgery. Cancer progression/recurrence will be defined as a measurable progression/recurrence documented on imaging.

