## 2.7 Study flow

Figure 1 shows the FARGO patient flow diagram. We expect that some of the eligible patients (group A) will undergo surgery without NACT. Group A will undergo only one preoperative study visit (baseline) within 45 days prior to their surgery. Patients undergoing NACT before their surgery (group B) will have a first baseline study assessment within 30 days prior to their first chemotherapy treatment; in this group, a second preoperative study visit will be repeated after chemotherapy is considered terminated at least 18 days post-chemotherapy cycle and within 45 days prior to surgery. Post-chemotherapy, a small proportion of patients will not be deemed eligible for surgery by the treating physician (group C). Group C will be only included in the evaluation of chemotherapy-related outcomes and then will leave the study. Group A and B will complete the study assessments and follow-ups. Some patients of group A and group B will undergo adjuvant chemotherapy after surgery; this will not affect their study timeline.

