### **4.2 Secondary clinical outcomes**

Secondary outcomes include:

- all cause death or new disability at 28 days and at 1 year after surgery;
- all cause death at 28 days, 6 months, and 1 year after surgery;
- disability at 28 days, 6 months, and 1 year after surgery;
- oncologic outcomes, including progression-free survival (PFS) and cancer-specific death, up to 1 year after surgery;
- major vascular complications (at 28 days, 6 months, and 1 year after surgery) defined as a composite of vascular death, and non-fatal myocardial infarction (or myocardial injury for the 28-day time point), stroke, symptomatic proximal venous thromboembolism, and cardiac arrest;
- infection, and infection with sepsis (at 28 days, 6 months, and 1 year after surgery);
- unplanned admission to ICU;
- length of stay;
- in-hospital delirium;
- postoperative cognitive changes at 6 months and at 1 year based on MoCA;
- chemotherapy-related outcomes, which include: tolerance as objectively defined by total dose received and time to completion; patient’s decisional regret (i.e., distress or remorse after a health

care decision, i.e., to undergo chemotherapy); change in health-related function or well-being (WHODAS 2.0); and change in cognitive performance (MoCA).

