## **5. FOLLOW UP**

### **5.1 Overall study**

Figure 2 shows the study participant timeline.

At baseline (i.e. before surgery, or before NACT for some cases), trained research personnel will collect relevant data about participant demographics, clinical and social history; will administer the WHODAS 2.0 questionnaire and the MoCA; and will assess for frailty. A trained clinical research assistant will measure frailty, first based on the CFS, and then administering the FP tests/questions. In patients undergoing NACT, the study personnel will repeat the frailty, WHODAS 2.0, and MoCA assessments before surgery, after the NACT is deemed to be terminated.

Study personnel will follow patients throughout their time in hospital for surgery, reviewing their medical records and recording any clinical outcome. In hospital, all patients will have troponin measured postoperatively, and then on the 1st, 2nd, and 3rd day after surgery or until discharge, whichever comes first. Data on ischemic symptoms/signs will be collected, and an ECG will be

performed if an elevated troponin measurement is detected. Data on any other troponin measurement that will be undertaken in any study participant within 28 days from surgery will be also collected and will be assessed upon the study definition for MINS. In hospital, study personnel will administer the 3D-CAM twice a day, during the first 3 days after surgery or until discharge, whatever comes first. We will use the CAM-ICU while the patients are in the Post-Anesthesia Care Unit (PACU) or if sent to ICU.

A follow-up study visit will be done at 28 days, 6 months, and 12 months after surgery. Efforts will be made to perform such study visits in concomitance with clinical follow-ups. Frailty assessments will be repeated at 28 days. WHODAS 2.0 will be administered at 28 days, 6 months and 12 months, in-person or over the phone, by research personnel blinded from the frailty assessments. MoCA will be administered at 6 and 12 months (in-person or through videoconference). Study personnel will also collect clinical outcome data through the study follow-ups.

We will also assess physicians' and patients' acceptability of frailty assessments (Appendix III).

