| Cognitive Assessment (MoCA)                   | X                                     | X                                  | X                                 |                        |                           | X                          | X                         |
| Troponin Measurement                          |                                       |                                    |                                   | X                      |                           |                            |                           |
| Disability Assessment (WHODAS 2.0)            | X                                     | X                                  | X                                 |                        | X                         | X                          | X                         |
| Delirium Assessment (3D-CAM)                  |                                       |                                    |                                   | X          |                           |                            |                           |
| Clinical Outcomes                             |                                       |                                    |                                   | X                      | X                         | X                          | X                         |
| Neoadjuvant Chemotherapy-related outcomes     |                                       |                                    | X                                 |                        |                           | X                          |                           |
| Blood Drawing for Biobanking                  | X                                     | X                                  | X                                 |                        | X                         | X                          | X                         |

 Should be done within 45 days prior to surgery  
 Refers to the round of chemotherapy closest to the surgery date  
 Should be done within 30 days prior to chemotherapy  
 Should be done at least 18 days post-chemotherapy cycle and within 45 days prior to surgery  
 Can be done in-person or by telephone/videoconference  
 Should be done twice a day

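### PFS is censored at the date last known alive although progression needs imaging, and the secondary NACT time origin contains survival time guaranteed by selection

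*Protocol*

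**What the plan says.** Protocol Appendix II, Oncologic outcomes, ends PFS follow-up for a patient without an event at the last date she was known to be alive: "or to the date of censoring at the last time the subject was known to be alive". It also says: "Cancer progression/recurrence will be defined as a measurable progression/recurrence documented on imaging". Death from any cause is an event.

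The same section sets two time origins. In the main one, "treatment initiation will be first defined as the time of surgery", paired with the pre-surgery frailty assessment. Then: "Secondarily, treatment initiation will be defined as initiation of any cancer-specific treatment, whether NACT or surgery", paired with the frailty assessment made before the first treatment.

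Four other places bear on this:

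- **Section 2.7**, on NACT patients who are not operated on: "Group C will be only included in the evaluation of chemotherapy-related outcomes and then will leave the study".
- **Section 4.2** sets the window: "oncologic outcomes, including progression-free survival (PFS) and cancer-specific death, up to 1 year after surgery".
- **Section 5.1**: "A follow-up study visit will be done at 28 days, 6 months, and 12 months after surgery". Footnote 5 to the Figure 2 schedule adds, for these visits: "Can be done in-person or by telephone/videoconference". The schedule has no imaging row.
- **Figure 2** marks clinical outcomes only from Day 0 after surgery. The post-NACT column has chemotherapy-related outcomes, and the Appendix II list of these does not include progression.

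**The concern.** The date last known alive is the natural censoring date for overall survival. For PFS it suits only an event that would be noticed whenever it happened. Here progression can be noticed only on a scan, while a telephone call is enough to extend follow-up. A patient scanned at month 6 and reached by telephone at month 12 contributes six months that nobody checked for progression.

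The second issue is the NACT origin. Time zero is the start of NACT, but entry to the analysis is decided later, by reaching surgery. The interval from NACT start to surgery therefore contains no deaths, by construction. Section 1.2.1 says, for ovarian cancer, that poor performance status and comorbidity typically lead to NACT. The guaranteed time is then likely to fall more on frailer patients and make frailty look less harmful than it is.

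**Working it through.** The protocol gives no PFS rate, event count, imaging frequency or cycle length, so there is no figure to reproduce. The definitions were set side by side as above, and the size was illustrated with assumed inputs. S(t) = 0.5^(t/median) throughout.

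**1. Censoring rule, absolute PFS.** Assume a share q has no imaging after month 6 but is known alive at month 12, and all PFS events are progressions. The protocol's rule then estimates

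S(6) × [q + (1 − q) × S(12)/S(6)] = S(12) + q × [S(6) − S(12)].

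| Median PFS (months) | True 12-month PFS | q = 10% | q = 20% | q = 40% |
|---|---|---|---|---|
| 12 | 50.0% | 52.1% | 54.1% | 58.3% |
| 18 | 63.0% | 64.6% | 66.3% | 69.5% |
| 24 | 70.7% | 72.0% | 73.4% | 76.1% |

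The overstatement is about 1 to 8 points. Where some events are deaths seen after scanning stops, it is smaller.

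**2. Censoring rule, frailty hazard ratio (Cox fits, 60,000 simulated patients, 30% frail).** With a true ratio of 1.80, non-frail median 18 months and no deaths:

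| Unscanned after month 6, frail / non-frail | Last known alive | Last imaging |
|---|---|---|
| 20% / 20% | 1.81 | 1.82 |
| 30% / 20% | 1.70 | 1.81 |
| 40% / 10% | 1.53 | 1.81 |

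With deaths included (true ratio 1.5, non-frail median 12 months, 20 to 50% of the PFS hazard being direct death, death after progression at 0.06 to 0.10 per month), 40% / 10% loss gives about 1.35 to 1.41 under the protocol's rule. Equal loss gives no bias in the ratio.

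In the same 40% / 10% setting, censoring at last imaging while keeping every later death as an event gives about 1.57 to 1.61. Frail 12-month PFS comes out at 31 to 32%, against a true 0.5^1.5 = 35%. It overshoots because later deaths are retained while later survivors are removed.

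**3. Length of the guaranteed interval.** Section 1.2.1 gives 3 to 4 NACT cycles. Figure 2 puts the second preoperative visit at least 18 days after a cycle and within 45 days before surgery. Assuming 21-day cycles:

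- First dose to preoperative visit, minimum: 2 × 21 + 18 = 60 days (3 cycles) or 3 × 21 + 18 = 81 days (4 cycles).
- Adding the full 45 days to surgery: 105 or 126 days.

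An interval t0 of 2 to 4 months is therefore reasonable.

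**4. NACT origin, absolute PFS.** If no event before surgery enters the analysis, 12-month PFS from NACT start is estimated as S(12)/S(t0).

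| Median PFS (months) | True | t0 = 2 months | t0 = 3 months | t0 = 4 months |
|---|---|---|---|---|
| 12 | 50.0% | 56.1% | 59.5% | 63.0% |
| 18 | 63.0% | 68.0% | 70.7% | 73.5% |
| 24 | 70.7% | 74.9% | 77.1% | 79.4% |

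For NACT patients the overstatement is about 4 to 13 points.

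**5. NACT origin, frailty hazard ratio (true 1.80, t0 = 3 months).** With 50% NACT use in both groups, the ratio is 1.83 without delayed entry and 1.82 with it. With 70% use in frail and 40% in non-frail patients, it is 1.65 without and 1.81 with delayed entry.

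**The case against.** Several points on the other side carry weight.

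- **Progression before surgery.** A reader might infer that NACT patients cannot have any PFS event before surgery. The documents support this only for death. The secondary definition would admit a progression imaged during NACT in a patient who is still operated on. Such events are merely not scheduled for capture in Figure 2. If they are recorded, the 4 to 13 points are too large.
- **Frailty and imaging.** A reader might infer that frail patients are followed by telephone, without scans, more often. No section says so. Remote visits are open to all, Section 5.1 asks that visits coincide with clinical follow-up, and scans belong to clinical care. Differential loss is an assumption, and without it the hazard ratio is not biased.
- **Size.** Ignoring deaths and assuming 40% / 10% loss, a true ratio of 1.5 falls to about 1.25. PFS includes deaths, and allowing for them roughly halves that shift. None of the simulations reverses the direction of the frailty effect.
- **NACT and frailty.** Section 1.2.1 speaks of performance status in ovarian cancer, not of measured frailty. The link is plausible but indirect.
- **Delayed entry belongs in an SAP.** Section 6.2 prescribes no risk set, so the omission alone is no fault. What stands is that the protocol itself fixes both the early origin and the removal of unoperated NACT patients, and that pair creates the guaranteed time.
- **Last-imaging censoring has its own bias.** This is correct, as step 2 shows, and the fix must allow for it.

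**Conclusion.** The point holds within limits. The censoring rule is stated outright and overstates absolute PFS wherever imaging stops before last contact. The size is about 1 to 8 points at 12 months under the assumed inputs, and less once deaths are counted. Bias in the frailty hazard ratio depends on unequal imaging loss, which the documents neither state nor exclude.

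In the NACT-origin analysis, survival to surgery is guaranteed by selection, and progression before surgery has no scheduled capture. Attenuation of the frailty association is probable but not certain. It requires NACT use to differ by frailty, and the fall from 1.80 to 1.65 rests on an assumed 70% / 40% split.

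The surgery-origin analysis has no guaranteed-time problem. PFS belongs to exploratory objective 7, so the primary AUC comparison and the sample size of 280 are unaffected. It is a correction that should be made, not one on which the study's main conclusion depends.

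**What to change.** 1. In Appendix II, censor patients without a PFS event at the date of the last imaging that showed no progression. State how a death long after the last scan is handled, and what happens to patients with no postoperative scan, who would otherwise be censored at time zero.
2. Report censoring at last known alive as a sensitivity analysis. The two rules can err in opposite directions, so agreement between them would be reassuring.
3. For the NACT origin, let patients enter the risk set at the date of surgery (delayed entry), describe the result as conditional on reaching surgery, and say how a progression documented before surgery is treated. Otherwise drop this analysis and keep surgery as the only origin.

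The cost is a few sentences of definition, scan dates recorded from the chart, and somewhat shorter PFS follow-up. Scan dates should be captured prospectively, since they may be hard to recover later.

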### **Chemotherapy-related outcomes**

They will include the following, measured at the end of any chemotherapy treatment (whether neo-adjuvant or adjuvant) when considered terminated:

1. Total dose received, defined as Relative Dose Intensity (RDI), as calculated as the percentage of the standard dose that was administered, using the formula below:  
Carboplatin RDI (%) = total dose administered / total standard dose \* 100  
Paclitaxel RDI (%) = total dose administered / total standard dose \* 100
2. Time to completion of all chemotherapy cycles, expressed as number of days.
3. Patient's decisional regret, defined as "distress or remorse after a (health care) decision," assessed using the Decisional Regret scale, a validated 5-item scale (Med Decis Making 2003; 23:281–292)
4. Change in health-related function or well-being, defined as the difference in WHODAS 2.0 score after chemotherapy compared to before chemotherapy.
5. Change in cognitive performance, defined as the difference in MoCA score after chemotherapy compared to before chemotherapy.

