| Follow-up            | 
Follow-up visits will be done (either by phone or in person) at 28 days, 6 months, and 1-year post-surgery. Efforts will be made to perform these visits in concomitance with clinical follow-ups. Frailty assessments will be repeated at the
                                                                                                                                                                                                                                                                                                                                                                                                                                                                                                                                                                                                                                                                                                                                                                                                                                                                                                                                                                                                                                                                                                                 |

|  |                                                                                                                                                                                                                               |
|--|-------------------------------------------------------------------------------------------------------------------------------------------------------------------------------------------------------------------------------|
|  | 28-day visit. WHODAS 2.0 will be administered at the 28-day, 6-month and 1-year visits. MoCA will be administered at the 6-month and 1-year visits. Study personnel will evaluate all study outcomes at each follow-up visit. |
|--|-------------------------------------------------------------------------------------------------------------------------------------------------------------------------------------------------------------------------------|

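### The chemotherapy-related MoCA change is defined for adjuvant treatment too, but no MoCA falls between surgery and month 6, so the adjuvant change also spans surgery

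*Protocol*

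**What the plan says.** Appendix II (Chemotherapy-related outcomes) lists five outcomes, to be "measured at the end of any chemotherapy treatment (whether neo-adjuvant or adjuvant) when considered terminated". The fifth reads: "Change in cognitive performance, defined as the difference in MoCA score after chemotherapy compared to before chemotherapy". The fourth defines the WHODAS 2.0 change in the same way. Section 4.2 also lists change in MoCA among the chemotherapy-related outcomes.

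The MoCA schedule is given in three places, and they agree:

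- **Study Summary, Follow-up:** "MoCA will be administered at the 6-month and 1-year visits".
- **Section 5.1:** MoCA at baseline. In patients having NACT, "the study personnel will repeat the frailty, WHODAS 2.0, and MoCA assessments before surgery", once NACT is finished. After surgery, MoCA at 6 and 12 months.
- **Figure 2, MoCA row:** marks at the preoperative assessment, before chemotherapy, after chemotherapy, 6 months and 1 year. The two chemotherapy columns stand under the heading for the period before surgery. The cells for days 0 to 3 and for the 28-day visit are empty.

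On chemotherapy given after the operation, Section 2.7 says: "Some patients of group A and group B will undergo adjuvant chemotherapy after surgery; this will not affect their study timeline".

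Figure 2 has one row for chemotherapy outcomes, labelled "Neoadjuvant Chemotherapy-related outcomes". It is marked at the after-chemotherapy assessment and at the 6-month visit.

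**The concern.** A before-and-after outcome needs one measurement shortly before the exposure and one after it. NACT patients have both. Patients treated after surgery have no MoCA between the operation and month 6, so their last score before chemotherapy is normally preoperative. The difference then contains whatever laparotomy, anaesthesia and recovery did to cognition, together with any change during chemotherapy.

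The protocol treats cognitive change after surgery as an outcome in its own right and plans to explore how well frailty predicts it (secondary objective 6). If the same difference is also reported under chemotherapy-related outcomes, an association between frailty and cognitive change after surgery could be presented as one between frailty and tolerance of chemotherapy. A later analysis plan cannot repair this, because the missing score is never taken.

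**Working it through.** No formula applies; the check is whether the schedule supplies the two scores that the definition needs.

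**Inputs.** The definition and its scope come from Appendix II. The MoCA times come from the Study Summary, Section 5.1 and Figure 2. The absence of extra visits for adjuvant treatment comes from Section 2.7. The treatment pathways come from Sections 1.2.1 and 2.7.

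**Available MoCA pairs by pathway**

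| Pathway | Last MoCA before the chemotherapy | First possible MoCA after it | What lies between |
|---|---|---|---|
| NACT (group B, before surgery) | Pre-NACT baseline | After NACT, before surgery | NACT only |
| Adjuvant, group A | Preoperative baseline | 6-month or 1-year visit | Surgery, recovery, adjuvant chemotherapy |
| Chemotherapy after surgery, group B | After NACT, before surgery | 6-month or 1-year visit | Surgery, recovery, postoperative chemotherapy |

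If the pre-NACT score were used in the third row, NACT itself would be added to the interval.

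**Condition.** The second and third rows assume that chemotherapy after surgery starts before the 6-month visit. The protocol gives no start date. Only a start after that visit would leave a scheduled MoCA between surgery and chemotherapy.

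**Overlap with another outcome.** Appendix II defines postoperative cognitive change as the 6-month or 1-year MoCA compared with the preoperative MoCA. For the second and third rows this is the same pair of scores, so one number would carry two labels and nothing in the data could separate them.

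**Timing of the later score.** Appendix II places the measurement at the end of chemotherapy. For adjuvant treatment the score comes from a visit fixed relative to surgery, which need not fall at that point.

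**Could another instrument fill the gap?** The 3D-CAM and CAM-ICU in the first three days assess delirium, not MoCA performance. WHODAS 2.0 is collected at 28 days, so the functional outcome has a possible postoperative starting value that MoCA lacks.

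**How many patients.** Section 2.3 expects at least 50% of 280 to have chemotherapy: 0.50 × 280 = 140. The split between neoadjuvant and adjuvant is not given. Purely as an assumption, if 30% to 70% of the 140 had adjuvant treatment only, that would be 0.30 × 140 = 42 to 0.70 × 140 = 98 patients. Section 1.2.1 describes the neoadjuvant pathway as including further cycles after surgery, so group B patients treated postoperatively would be affected in addition.

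**The case against.** The best case for leaving the plan alone has four parts.

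*The outcome is exploratory.* Section 2.3 describes the chemotherapy analyses in those terms. Secondary objective 3 concerns prediction rather than the causal effect of chemotherapy, and its list of outcomes does not name cognition. All of this is correct and limits the weight of the point. It does not make the adjuvant change a chemotherapy-related change, which is what Appendix II calls it.

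*Pooling is not stated.* A reader might infer that neoadjuvant and adjuvant changes will be analysed together. The protocol does not say so: Section 6.2 leaves the models for these outcomes to be chosen as appropriate, and the choice between pooling and separating may sit in an analysis plan that is not shown. That objection stands. The mislabelling does not depend on pooling, because even a separate adjuvant analysis would use a difference that spans surgery.

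*Figure 2 does not stop adjuvant data collection.* From the row label "Neoadjuvant Chemotherapy-related outcomes" a reader might infer that sites would record no dose, duration or regret data in adjuvant-only patients. The documents do not support that. The row is marked at the 6-month visit, in the block for all patients. The separate clinical outcomes row is marked at every postoperative time, and Appendix II orders collection after adjuvant treatment. What remains is a label narrower than the definition it serves.

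*The size of any distortion is unknown.* It is tempting to set a supposed surgical effect of one MoCA point against the two-point cut-off in Appendix II. The one-point effect would be an assumption, and the cut-off defines decline in an individual for a different outcome. The comparison would not measure bias and is not relied on here.

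**Conclusion.** The point holds for the MoCA change outcome in patients who have chemotherapy after surgery, whether in group A or group B. As scheduled, their change covers surgery plus chemotherapy and coincides with the postoperative cognitive outcome. It should be neither described as chemotherapy-related nor combined with the NACT change, which is sound. The conclusion rests on one assumption, that postoperative chemotherapy begins before the 6-month visit.

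The numerical effect on any estimate cannot be stated from the protocol. The reach is one of five chemotherapy-related outcomes, in an unstated share of at least 140 patients. The primary outcome, sample size and primary analysis are untouched. The matter is worth correcting, but it does not threaten the study's main conclusion.

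**What to change.** 1. In Appendix II, limit the chemotherapy-related MoCA change to the pair taken before and after NACT.
2. Report the MoCA change in patients treated after surgery separately, under a name such as *change after surgery plus adjuvant chemotherapy*, and state that it uses the same scores as postoperative cognitive change.
3. For the WHODAS 2.0 change in adjuvant patients, use the 28-day score as the starting value only when that visit precedes the first adjuvant cycle. Note that this score may still reflect early postoperative disability, so later recovery could mask a decline during chemotherapy.
4. Remove the word Neoadjuvant from the chemotherapy row label in Figure 2 so that it matches Appendix II. The 6-month visit is already marked.

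The cost is wording, plus fewer patients in one exploratory secondary analysis. No new visit or test is needed.
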